### Intervention

The self-management group intervention will involve eight 90-minute sessions held at weekly intervals at a memory clinic in North Wales. It will be led by two members of the clinical team who will be trained to administer the intervention by the research team, with ongoing access to support during the study. Up to seven people with dementia will attend each group, and caregivers (a relative or friend of each participating person with dementia) will be invited to attend the first and final sessions. Caregivers may also, if they wish, join the group at the end of each meeting to hear an overview of the theme that has been covered. Participants will be invited to share only personal information that they are comfortable disclosing during the self-management group. Each attendee will receive a booklet which will cover the content of each session: this will allow space for additional notes and comments to be made and the person with dementia can share this resource with the caregiver between sessions. Participants attending the self-management group will continue with all other care services they are receiving.

There will be a flexible approach to the organisation and structure of sessions. Each session will cover a particular theme and participants will discuss the theme with each other and the facilitators. Within each theme participants will be able to focus on aspects that are meaningful to group members. Session themes will cover an orientation to the group and information sharing, enjoying hobbies, activities and interests, staying well, practical ways to manage memory difficulties, maintaining relationships and social networks, planning for the future, coping skills and accessing local resources. The group will be facilitated in an informal manner and time will be provided for more social activities. The facilitators will keep a record of the number of intervention sessions attended by each participant. The facilitators will also write a summary of each session incorporating their impressions of participants’ involvement in the meeting.

### Comparison condition: treatment as usual

Participants randomised to TAU will continue to receive the normal services provided by the memory clinic. These services include a regular nurse-led clinical review and access to services such as psychiatry, occupational therapy and social services as needed. Using TAU as a comparator condition ensures that all participants receive needed services.

### Procedure

Potential participants will be invited to take part via an invitation letter or via personal contact from a member of the clinical team. Posters and leaflets advertising the study will be displayed at the memory clinic and groups that make use of the service facilities, such as the local Alzheimer’s café, will receive information about the study. As this is a pilot study, a range of recruitment methods is envisaged to inform future multi-centre trials. People interested in taking part will be contacted by a researcher who can provide more information about the study and answer any questions. If the person is interested in taking part in the study the researcher will arrange a meeting. If the person consents to take part in the study, the researcher will make final eligibility checks and carry out the baseline assessments. Participants will be allowed to pace these assessment visits according to their needs. For instance, short breaks will be permissible if participants are fatigued and if necessary two visits will be made to complete the assessments at each data point.

Eligible, consenting participants will be randomised to receive either the self-management group intervention or TAU after baseline assessments. Randomisation will be conducted by the North Wales Organisation for Randomised Trials in Health (NWORTH). Randomisation will be undertaken using a computer-based algorithm. Randomisation will be balanced (one: one dynamic allocation) [51] and will be stratified for mini-mental state examination score (20 to 24, 25 to 25+) and gender.

Follow-up assessments will occur at 3 and 6 months post-randomisation and will be undertaken by a researcher blinded to group allocation. There will be no unblinding of the researcher, and participants will be asked not to tell the researcher whether they attended the group. To assist retention in the study, appointments will be prescheduled with participants, and reminders of upcoming meetings will be sent. Participants who attend the self-management group will additionally be invited to take part in a post-intervention interview to feed back their experiences of attending the group.

### Analysis

Data will be entered into IBM SPSS Statistics v20 and checked to ensure that accuracy is within acceptable limits. Participants who have completed assessments for at least two data points will be included in the analysis. All available data will be included and an intention-to-treat analysis will be conducted. If an outcome measure has less than 20% missing responses, missing data will pro-rated with the participant’s mean item score to allow a calculation of the total score. If an outcome measure has more than 20% missing responses, methods of multiple imputation will be explored and a range of sensitivity analyses will be performed to inform the main RCT. As this is a pilot study all outcomes will be reported and particular note will be taken of effect sizes and confidence intervals.

Analysis of covariance (ANCOVA) using baseline scores and stratification variables as covariates will compare group outcomes with regard to the primary outcome, the self-efficacy scores of people with dementia at 3 months post-randomisation. Secondary outcomes will be analysed similarly and confidence intervals will be quoted for all parameter estimates. The Bonferroni correction for multiple testing will not be made as this is a pilot exploratory study to estimate potential effect sizes rather than a strictly hypothesis-testing experimental design. The post-intervention interviews will be analysed using thematic analysis to explore and summarise participants’ experience of the intervention. This analysis will be undertaken independently by members of the research team. Inter-rater reliability will be addressed by having a random selection of 20% of transcripts coded by two raters so that differences can be discussed and resolved. If inter-rater reliability reaches 80% or more, then the remainder of transcripts can be coded by a single rater. If not, a further 20% of transcripts will be coded by both raters and the process repeated.

An economic evaluation will investigate the incremental cost-effectiveness of the self-management group compared with TAU. Costs for the group will be calculated from a public-sector multi-agency perspective. Primary and secondary care health service use will be collected using the CSRI and costs will be calculated using national unit costs [52,53]. A cost-utility analysis using the EQ-5D-3L will generate a cost per quality-adjusted life-year and cost-effectiveness acceptability curve for comparison with the National Institute for Health and Care Excellence ceiling of £20,000 to £30,000 [54]. A secondary exploratory cost-effectiveness analysis will be undertaken using the GSES and ICECAP-O as the measures of effectiveness. As this is a pilot trial with a relatively small sample size, the tree-age modelling package will be utilised to map a decision analytic model to inform data collection for the economic evaluation of a future definitive multi-centre study.

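### The two-data-point entry rule drops randomised participants on a post-randomisation event, so the analysis set is not the intention-to-treat set the plan says it is

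*Protocol article*

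**What the plan says.** All the relevant statements are in the protocol article.

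- **Timing (Procedure).** "Eligible, consenting participants will be randomised to receive either the self-management group intervention or TAU after baseline assessments". Then: "Follow-up assessments will occur at 3 and 6 months post-randomisation".
- **Analysis set (Analysis).** "Participants who have completed assessments for at least two data points will be included in the analysis".
- **Declared principle (Analysis, the next sentence).** "All available data will be included and an intention-to-treat analysis will be conducted".
- **Missing data (Analysis).** For a measure with less than 20% of responses missing, "missing data will pro-rated with the participant’s mean item score to allow a calculation of the total score". Above that: "If an outcome measure has more than 20% missing responses, methods of multiple imputation will be explored", together with sensitivity analyses that are not described.
- **Primary analysis (Analysis).** "Analysis of covariance (ANCOVA) using baseline scores and stratification variables as covariates will compare group outcomes with regard to the primary outcome", the outcome being GSES at 3 months.

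The planned sample is 42 people with dementia allocated 1:1, or 21 per arm. No expected attrition is stated; retention is one of the things the pilot is meant to measure.

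**The concern.** Intention-to-treat requires that membership of the analysis set be settled by randomisation. Here it depends on attending at least one follow-up visit. Attendance can differ by arm, because one arm is asked to come to eight weekly 90-minute sessions and the other continues with usual services. If it does differ, and those lost would have scored differently, the comparison among those retained is no longer the randomised one.

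What is at stake is the estimate, not a confirmatory test. The article describes the trial as exploratory and intends its effect sizes and confidence intervals to inform the power of a full trial. An estimate labelled intention-to-treat that is really available-case would be carried into that planning with more authority than it has earned. With 21 per arm, each person dropped is 1/21, about 5%, of an arm.

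**Working it through.** **1. Which follow-up patterns the rule admits.** Baseline precedes randomisation, so every randomised participant has it.

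| Baseline | 3 months | 6 months | Data points | Meets rule | 3-month GSES for the primary ANCOVA |
|---|---|---|---|---|---|
| yes | yes | yes | 3 | yes | observed |
| yes | yes | no | 2 | yes | observed |
| yes | no | yes | 2 | yes | missing; used only if imputed |
| yes | no | no | 1 | **no** | excluded by the rule |

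The fourth row is the contradiction: a randomised person with available baseline data is left out of an analysis described as using all available data by intention-to-treat. The third row is a separate weakness: the person is in the set, but the plan only undertakes to look into the imputation that would supply the primary outcome.

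**2. The plan's own figure.** The sample of 42 is consistent with 3 waves × 14 = 42 and with 42/2 = 21 per arm. No power inputs are given, so no more can be reproduced.

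**3. How many could be excluded.** The share lost with baseline only, d, is an assumption. Number analysed n = 42 − round(42d); standard error multiplier = √(42/n).

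| d (assumed) | Excluded | Analysed | SE multiplier |
|---|---|---|---|
| 10% | 4 | 38 | √(42/38) = 1.05 |
| 20% | 8 | 34 | √(42/34) = 1.11 |
| 30% | 13 | 29 | √(42/29) = 1.20 |

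**4. How far the estimate could shift.** In an arm with lost share q, the mean over all randomised is (1 − q) × retained mean + q × lost mean. The retained mean therefore differs from it by q × gap, where gap is retained minus lost, in SD. With a common gap, the between-arm shift is (q_group − q_TAU) × gap. Because the planned analysis is an ANCOVA, gap must be read as what remains after adjustment for baseline and the stratification variables. All values are assumed.

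| Loss, group v TAU | Gap 0.25 SD | Gap 0.5 SD | Gap 1.0 SD |
|---|---|---|---|
| 10% v 10% | 0 | 0 | 0 |
| 20% v 10% | 0.025 | 0.05 | 0.10 |
| 30% v 10% | 0.05 | 0.10 | 0.20 |
| 30% v 5% | 0.06 | 0.125 | 0.25 |

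**5. What the rule adds beyond the missing data.** A simulation assumed 21 per arm, baseline–outcome correlation 0.6, a true effect of 0.5 SD and about 20% loss in the group arm only (4,000 runs, Monte Carlo error 0.004).

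- Loss depending on baseline: bias 0.10 SD unadjusted, 0.004 for the ANCOVA without the lost people, and 0.004 after multiple imputation of all 42.
- Loss depending on the unseen outcome: 0.095 for the ANCOVA and 0.096 after multiple imputation of all 42.

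The size of these biases depends on the assumed loss mechanism. The agreement between ANCOVA and imputation is to be expected: for someone with no outcome after baseline, imputation from the ANCOVA's own covariates brings in no new information about the arm contrast.

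**The case against.** The strongest reply is that the conflict is mainly one of labelling. The rule removes only people who have no outcome at all. For them, imputation under missing-at-random scarcely moves the primary estimate, as step 5 shows. The trial is an exploratory pilot, retention will be recorded, some sensitivity analyses are promised, and imputation detail is commonly left to a statistical analysis plan. Much of this stands, and it limits how hard the point can be pressed. It does not remove the point: the article does not leave the analysis set open. It fixes one, and then gives it a name that the rule contradicts.

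Three stronger readings are tempting and are not supported.

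- *Baseline-only participants cannot be imputed.* A reader might infer this from the order of the sentences, but the article does not confine imputation or the sensitivity analyses to the admitted set. Baseline GSES, MMSE band and gender would be available. It is fair to say only that nothing in the text brings these people back.
- *Someone with baseline and 6 months is lost to the primary analysis.* On a natural reading, a wholly missing 3-month GSES exceeds the 20% threshold and so falls under the imputation clause. The weakness is the lack of commitment.
- *The rule inflates the effect by a known amount that its deletion would cure.* With 20% loss in the group arm, none in TAU, and a gap of 0.5 to 0.8 SD, the shift is 0.20 × 0.5 = 0.10 to 0.20 × 0.8 = 0.16 SD, or 20% to 32% of an assumed 0.5 SD effect. That is an unadjusted, one-sided worst case. It is produced by informative loss, and neither a missing-at-random model nor imputation would remove it for baseline-only people.

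**Conclusion.** The point holds as a contradiction within the document. The two-data-point rule selects on a post-randomisation event, so the resulting set is neither intention-to-treat nor all available data. This follows from the timing of baseline and randomisation alone and needs no assumption.

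Its numerical consequence cannot be fixed from the article. The shift is nil when loss and adjusted gap are equal across arms. It is about 0.03 to 0.25 SD for assumed loss between 20% v 10% and 30% v 5% with a gap of 0.25 to 1.0 SD. Those figures describe the missingness; the rule conceals it under the wrong label more than it creates it. The severity is moderate: the affected estimate is exploratory, but providing it for the full trial is the purpose of the pilot.

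**What to change.** 1. Delete the two-data-point rule and define the intention-to-treat set as all randomised participants, analysed as allocated.
2. Commit to a method for missing 3-month GSES: multiple imputation using baseline, 6-month score, arm, MMSE band and gender, or an equivalent likelihood-based model. The ANCOVA can remain the primary model; moving to a longitudinal model is optional.
3. Add sensitivity analyses in which lost participants are allowed to differ from retained ones, separately by arm (missing not at random). Only this step addresses informative loss.
4. Keep the available-case ANCOVA as a comparison labelled as such, and report exclusions by arm.

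The minimum acceptable change is to stop calling the two-data-point set intention-to-treat, label it available-case or modified, and report exclusions by arm.

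The cost is a few sentences and a little extra programming, with no new data. The gain should not be oversold: for baseline-only participants, missing-at-random imputation adds little to the primary estimate. The benefit lies in a properly defined randomised set, the use of 6-month scores where the 3-month score is missing, and a base for the sensitivity analyses.

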### Setting and participants

The aim is to recruit 42 people with early-stage dementia and their primary caregivers. The study will proceed in three waves with approximately 14 participants in each wave. The sample size will provide adequate statistical power for a pilot evaluation of the self-management group, and decisions about sample size have been informed by the need to balance the number of participants required to provide an appropriate amount of information for a pilot study with the number that it is feasible to recruit within the study timescale. As this is a pilot trial, particular note will be taken of recruitment and retention rates so that a future definitive study may be accurately powered. All participants will need to provide informed consent. In order to be deemed to provide informed consent, participants will have to demonstrate that they can understand the study information, retain and weigh up this information sufficiently to clearly communicate their decision about participation, and clearly understand the consequences of this decision.

Participants will be identified from a memory clinic in a semi-rural area of North Wales. The inclusion criteria for people with dementia are as follows: 1) participants must be diagnosed with Alzheimer’s, vascular or mixed Alzheimer’s and vascular dementia, according to ICD-10 criteria [29] and in the early stages as indicated by a score of 20 or more on the Mini-Mental State Examination [30]. These diagnoses account for 89% of dementia diagnoses [31] and rarer sub-types of dementia have been excluded here because they involve features that would require a specific approach; 2) participants must be able to provide informed consent; 3) participants may be either taking or not taking acetyl-cholinesterase inhibitors or Memantine. Participants receiving acetyl-cholinesterase inhibitors or Memantine must have been stabilised on their current dose for a minimum of one month prior to baseline assessment, with no plan to change dosage or medication during the course of the study. This is to ensure that change is not confounded by medication effects, and 4) participants must have a caregiver who is willing to participate in the study. Caregivers may be spouses, partners, siblings or adult children of people with early-stage dementia who are involved in providing day-to-day support.

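### The ANCOVA treats all participants as independent although the intervention is delivered in about three groups of up to seven, so its confidence intervals are too narrow for any positive within-group correlation

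*Protocol article*

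**What the plan says.** The Setting and participants section gives the size and staging: "The aim is to recruit 42 people with early-stage dementia and their primary caregivers", and "The study will proceed in three waves with approximately 14 participants in each wave". The Procedure section describes individual randomisation in a one-to-one ratio, which "will be stratified for mini-mental state examination score (20 to 24, 25 to 25+) and gender".

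The Intervention section describes group delivery over eight weekly sessions: "Up to seven people with dementia will attend each group", and "Each session will cover a particular theme and participants will discuss the theme with each other and the facilitators". Each group has some freedom to concentrate on what matters to its members. The comparator section describes ordinary memory clinic services, with no group element.

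The Analysis section fixes the model: "Analysis of covariance (ANCOVA) using baseline scores and stratification variables as covariates will compare group outcomes with regard to the primary outcome". It continues: "Secondary outcomes will be analysed similarly and confidence intervals will be quoted for all parameter estimates". Neither that section nor the sample-size text mentions clustering by treatment group or an ICC. The abstract names parameter estimates and confidence intervals as what the pilot is to supply, so that a full trial can be powered.

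**The concern.** People treated in the same group share facilitators, peers and discussion for eight weeks, so their outcomes may be more alike than those of people in different groups. Nothing comparable links participants in usual care. This is a partially nested design, with clustering in one arm only.

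The stated ANCOVA assumes independent residuals throughout. If outcomes are positively correlated within groups, the mean of the intervention arm is less precise than the model believes, and the interval for the treatment difference is too short. The same holds for the secondary outcomes, which use the same approach. Because the intervals are a main product of the pilot and are meant to inform a larger trial, overstated precision could be carried forward.

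This is not a detail that a condensed article leaves to a fuller document. The article names the model and its covariates, and that model omits the group.

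**Working it through.** **Inputs from the document.** 42 participants; three waves of about 14; one-to-one allocation; at most seven per group; ANCOVA on baseline score, MMSE band and gender.

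**Implied structure.** 3 × 14 = 42. One-to-one allocation gives 14 / 2 = 7 per arm per wave, hence about three intervention groups of seven (21 people) against 21 in usual care. The document does not state three groups. Wave is not a stratification factor, so actual group sizes may differ.

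**Input not in the document.** The ICC. It is an assumption, taken here over the range 0 to 0.20.

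**Formulas.** With m = 7 per group, equal arms and equal total variance in both arms:

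- design effect in the intervention arm = 1 + (m − 1) × ICC = 1 + 6 × ICC
- effective intervention-arm size = 21 / (1 + 6 × ICC)
- true SE / reported SE of the difference = √{[(1 + 6 × ICC) + 1] / 2}
- shortfall of the reported SE = 1 − 1 / ratio

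For ICC 0.10: the design effect is 1.60, the ratio is √(2.60 / 2) = 1.14, and the shortfall is 1 − 1/1.14 = 12%.

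The last column is the coverage of the nominal 95% interval when the stated ANCOVA is simulated (baseline plus two binary strata, 37 residual degrees of freedom, 10,000 trials per ICC).

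| Assumed ICC | Design effect | Effective n (of 21) | True SE / reported SE | Reported SE too small by | Simulated coverage |
|---|---|---|---|---|---|
| 0 | 1.00 | 21.0 | 1.00 | 0% | 95.0% |
| 0.02 | 1.12 | 18.8 | 1.03 | 3% | 94.5% |
| 0.05 | 1.30 | 16.2 | 1.07 | 7% | 93.3% |
| 0.10 | 1.60 | 13.1 | 1.14 | 12% | 92.0% |
| 0.20 | 2.20 | 9.5 | 1.26 | 21% | 88.0% |

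**Attrition.** With five per group in place of seven, and arms still equal, the ratios are √[(1.20 + 1) / 2] = 1.05 at ICC 0.05 and √[(1.40 + 1) / 2] = 1.10 at ICC 0.10.

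**Can the group variance be estimated instead?** Three groups give 2 degrees of freedom between groups, and three groups of seven give 18 within. The ANOVA estimate of the group variance is zero or negative when the F ratio is below 1. This has probability 1 − (1 + 2x/18)^(−9), with x = (1 − ICC) / (1 + 6 × ICC).

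- ICC 0.05: x = 0.95 / 1.30 = 0.731, probability about 50%.
- ICC 0.10: x = 0.90 / 1.60 = 0.5625, probability about 42%.

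So in about half of such trials at ICC 0.05 a random-effects model would return essentially the plain ANCOVA standard error. An analysis of the three group means with Satterthwaite degrees of freedom does not solve this either. At ICC 0.05 its mean half-width was 0.77 residual SD against 0.64 for the ANCOVA (0.77 / 0.64 = 1.20, or 20% wider), with coverage of only about 92%.

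**The case against.** The strongest reply is that the size of the error is unknown and may be small. The document gives no ICC; at 0.02 coverage is still 94.5%, and attrition reduces the effect further. Beside the imprecision of 21 per arm this is a minor loss. That stands as a limit on size. It does not remove the point, because the interval is right only if the ICC is zero, and interactive group delivery gives reason to doubt that.

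Second, the Analysis section presents the study as exploratory and not strictly hypothesis-testing. No decision rests on a p-value, and under the assumptions above clustering does not bias the point estimate. That also stands, and it is why this is not a fatal flaw. The intervals, however, are a declared product of the pilot.

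A reader might infer three stronger things that the documents do not support:

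- **That the intervals are known to be too narrow by a given amount.** The amount depends wholly on an assumed ICC.
- **That the full trial will be planned without a design effect.** Nothing says so. The article is only silent on the matter.
- **That a partially nested mixed model should replace the ANCOVA.** Three groups cannot estimate the group variance usefully, as shown above, and an ICC estimated here would be too imprecise to size a trial.

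**Conclusion.** The concern holds in conditional form. The document's own figures imply about three intervention groups of about seven against about 21 individually treated participants, and the stated model ignores that structure. For any positive within-group ICC the reported 95% intervals are too narrow: slightly at 0.02 to 0.05, and materially from about 0.10, where the reported SE is 12% too small and coverage about 92%.

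These sizes rest on equal groups of seven, equal total variance in the two arms and an assumed ICC. The point should be fixed, but it is not critical, since the pilot is exploratory and has no decision rule that depends on significance.

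**What to change.** Keep the ANCOVA and its point estimate, and amend the Analysis section as follows:

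1. State that the design is partially nested, and record which group each intervention participant was assigned to.
2. For primary and secondary outcomes, report the confidence interval with the intervention-arm variance inflated by 1 + (m − 1) × ICC at fixed ICCs of 0, 0.05 and 0.10, taking m from the actual group sizes. Describe the ICC = 0 interval as a lower bound on the uncertainty.
3. Report any estimated ICC as descriptive only, and do not make a mixed model with an estimated group variance the primary analysis.
4. When the pilot's results are used to power the full trial, use the inflated intervals and allow for clustering.

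The cost is analysis wording and one recorded variable; facilitators already log each participant's attendance. Recruitment and allocation do not change. The intervals become about 7% wider at ICC 0.05 and 14% wider at ICC 0.10, and each has close to its nominal coverage only if the assumed ICC is about right.
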